## Abstract

**Background:**

The responsibility of care for Veterans and Service Members (V/SMs) with traumatic brain injury (TBI) often defaults to informal family caregivers. Caregiving demands considerable knowledge, skill, and support to facilitate the health and well-being of V/SMs and themselves. Persistent and common TBI caregiver issues include strain, depression, and anxiety. While evidence-based, brief interventions have been developed and implemented for family caregivers in Veteran neurodegenerative populations, few interventions have been developed, adapted, or tested to support the unique needs of caregivers of V/SMs with TBI.

**Objective:**

This study will adapt and test an evidence-based, personalized, 6-session telehealth caregiver intervention, “Resources for Enhancing All Caregivers’ Health” (REACH), to meet the unique needs of caregivers of V/SMs with TBI. If successful, a community-based participatory research team will develop an implementation plan to roll out REACH TBI across the national Veterans Affairs Polytrauma System of Care.

**Methods:**

This mixed methods, crossover waitlist control clinical trial will use a Type 1 Hybrid Effectiveness-Implementation approach to adapt and then test the effects of REACH TBI on key TBI caregiver outcomes.

**Results:**

This study was funded by the Department of Defense in September 2023. Participant enrollment and data collection will begin in 2024.

**Conclusions:**

If effective, REACH TBI will be the first evidence-based intervention for caregivers of V/SMs with TBI that can be scaled to implement across the Veterans Affairs Polytrauma System of Care and fill a notable gap in clinical services.

**International Registered Report Identifier (IRRID):**

PRR1-10.2196/57692

## Introduction

Between 2000 and 2021, a total of 444,328 US military Service Members were diagnosed with traumatic brain injury (TBI) [1], leading to TBI’s designation as the “signature injury” of Operation Enduring Freedom (OEF), Operation Iraqi Freedom (OIF), and Operation New Dawn [2,3]. Between 7% and 23% of OEF/OIF/Operation New Dawn-era Veterans and Service Members (V/SMs) have experienced a TBI [2-5]. In 2009, the annual health care costs for OEF/OIF Veterans with TBI were almost 4 times higher than those without TBI (US $5831 vs US $1547), and the highest costs (US $7974) were shown in those with TBI, pain, and posttraumatic stress disorder (Taylor et al [5]). V/SMs receiving services in the Veterans Affairs (VA) have over 93,000 documented TBIs [6]. TBI can result in a constellation of long-term physical, cognitive, and neurobehavioral impairments [7-10]. Recovery time is variable, and many symptoms remain years or decades after injury, especially with more severe injuries [11]. As a result of these long-term consequences and care needs, rehabilitation medicine now unequivocally considers TBI a chronic health condition requiring long-term management and support [12].

Informal family TBI caregivers experience a myriad of unmet emotional, instrumental, and professional support needs regarding symptom management [13], and research has shown these high rates of unmet needs are closely associated with mental health problems in caregivers [14]. Caregivers often receive little formalized training or support in caregiving and symptom management, and physical symptoms in individuals with TBI are associated with greater family household needs, and emotional symptoms with greater family informational needs [15]. Among caregivers of V/SMs with TBI, over 40% of their needs go unmet with caregiver peer support, respite from caregiving, and help with caregiver negative emotions being the least often met needs; greater environmental barriers keeping the V/SM from participating in activities and the presence of V/SM mental health issues translate into more unmet emotional, community, and professional support needs [16]. Despite some parallels to civilian populations with TBI, V/SMs can have unique features of TBI (eg, polytraumatic and blast-related) and high rates of particular comorbid conditions (eg, posttraumatic stress and pain) that impact V/SMs’ health and needs [17-19] and may require additional and unique caregiving skills. Few military family members expect to provide the sort of long-term care that may be required by these complex injuries [20], and lack of training or formal support can compound caregiver strain and emotional distress [21]. Over time, military TBI caregivers experience declines in physical and mental health [22], reporting worse health than the general population [23]. Higher levels of TBI symptoms experienced by V/SMs are associated with greater caregiver strain and distress [24], which are in turn associated with caregiver grief and depression [24,25].

At present, there is no standardized, evidence-based, and widely implemented intervention for caregivers of V/SMs with TBI. Thus, there is a significant need for an evidence-based, portable caregiver telehealth intervention that is (1) adapted to TBI-specific needs, (2) relevant to caregivers of younger V/SMs with a range of neurobehavioral symptoms and strong potential for a positive recovery trajectory, and (3) readily accessible in rural and resource-limited communities. Resources for Enhancing All Caregivers’ Health (REACH) VA [26] is a successful evidence-based, 4- or 6-session telehealth behavioral intervention for caregivers and a VA national program for dementia [27], spinal cord injuries and disorders [28], multiple sclerosis [29], and posttraumatic stress disorder caregivers [30]. REACH has never been tailored specifically for or tested in caregivers of V/SMs with TBI. This study protocol describes the adaptation, evaluation, and implementation of a telehealth intervention, REACH TBI, for caregivers of V/SMs with TBI during the chronic phase of recovery.

## Methods

### Study Design

This study is a prospective mixed methods (greater emphasis on quantitative over qualitative data), type 1 Hybrid Effectiveness-Implementation study [31,32], with a crossover waitlist control clinical trial [33]. This is a multi-aim, multi-phase, VA-wide clinical trial that will include (1) engagement with caregivers of V/SMs with TBI and Polytrauma System of Care (PSC) clinicians to inform REACH adaptation for TBI, (2) a national waitlist control clinical trial, (3) development of an ambitious PSC implementation plan, and (4) a foundational community-based participatory research (CBPR) approach with stakeholders throughout every phase. Human-centered design (HCD) is a 5-step guiding framework integrating the study’s 3 aims and overall methodology and is fundamentally about identifying and responding to human needs [34]. As applied to implementation science in health care, studies based upon it often attempt to (1) develop an understanding of people and their needs, (2) engage stakeholders from early on and throughout the design process, and (3) adopt a systems approach to address systematical interactions among the micro, meso, and macro levels of health care [34]. During the initial HCD Discover and Define phases, interviews will be conducted with intended users and stakeholders (eg, TBI caregivers and PSC clinicians). These interviews will construct a narrative of TBI caregiver needs, engage intended users in meaningful discussion about REACH TBI appropriateness, and identify likely implementation facilitators and barriers. Ideas, emerging themes, and recommendations generated will help transition to the Design phase. The Design phase will inform REACH TBI optimization to meet the unique needs of caregivers of V/SMs with TBI. The Validate phase will test the effectiveness of REACH TBI nationally and support the Implementation phase when we develop an implementation plan to roll out REACH TBI across the PSC in a successive grant. As is consistent with the HCD, evaluation, progress, and milestone assessments will ensure process and outcome measures are met. The study is expected to recruit over 18 months.

### Setting

There are 4 research cores in this multicenter study. The University of Virginia (UVA; Charlottesville, Virginia) is the administrative core responsible for overseeing and directing the clinical trial in collaboration with multiple principal investigators leading the other 3 study cores. The James A. Haley Veterans’ Hospital (Tampa, Florida) is the data core where recruitment and data collection will be conducted. Virginia Commonwealth University (Richmond, Virginia) is the intervention core where the REACH TBI intervention will be delivered via telehealth. The University of Utah (Salt Lake City, Utah) is the implementation core where evidence-based strategies will be developed to implement REACH TBI throughout the VA PCS. Additionally, the University of Tennessee Health Science Center Caregiver Center (Memphis, Tennessee) will inform intervention protocol development and train REACH TBI interventionists.

### Intervention Development

Central to our team is the VA National Caregiver Center to leverage the foundational REACH [35] intervention—including its associated tools (eg, Caregiver Notebook and Risk Assessment), trainings, and delivery resources (Coach Manual [36] with scripts and checklists)—to accelerate a deployable REACH TBI protocol for clinical trial testing within 6 months of grant commencement. During the first 6 months of the grant timeline, adapting REACH for TBI will include extensive qualitative assessment involving CBPR engagement with subject matter experts (SMEs) and research team members throughout the PSC including caregivers of V/SMs with TBI, clinicians, clinical researchers, and administrators.

### Participants, Recruitment, and Sample Size

The eligibility criteria for V/SMs with TBI and caregivers are the following: (1) age of 18 years and older; (2) English-speaking; (3) primary caregiver for a V/SM who sustained a TBI at least 6 months prior; (4) primary caregiver who has provided care for a V/SM with TBI for at least 6 months; (5) provide some level of daily supervision or assistance with either a physical, cognitive, or behavioral issue they think is likely related to TBI; (6) believe that at least half of their caregiving responsibilities are likely related to TBI rather than another health condition or conditions; and (7) endorse a score of at least high burden (a score of 8 or higher) on the Zarit Burden Inventory-4 [37]. The exclusion criteria are (1) no access to the telephone or internet-accessible device, (2) auditory impairment that would make telephone use difficult, and (3) have completed a previous version of the REACH intervention. Participants had to report some level of burden associated with caregiving [35] based on prior research showing that burdened caregivers were more likely to benefit from the REACH intervention [38]. These criteria have been used successfully in caregiver studies to identify a stressed population.

A power analysis was completed to determine the number of participants necessary to achieve 80% power on the primary outcome assuming 10% attrition [39]. Baseline scores will be used as a covariate in the model as this increases statistical power, given that baseline and follow-up scores are usually highly correlated, resulting in a reduction in the error term of the model [40]. Assumptions used in computations included equal sample sizes in each contrast group, equal variances and attrition, probability of type I error of .05, and 2-sided testing of the null hypotheses [41]. Accordingly, 55 participants will be randomized to each group (N=110). With this sample size, we will have 80% power to detect a Cohen *d* of 0.50 assuming a correlation of pre- and postintervention scores of 0.50.

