### Randomization

A block randomization schedule [42] (with 6 participants per block) will be created with a web-based computerized random number generator. The UVA research coordinator will maintain allocation concealment and eliminate possible selection or recruitment biases by keeping the randomization schedule concealed from the on-site research coordinator engaged in recruiting. The randomization schedule will be generated by the UVA research coordinator who will not have any contact with participants, and sequentially numbered sealed envelopes will be prepared prior to the recruitment of any participants. After the recruiting research coordinator determines eligibility for a prospective dyad and obtains informed consent, the UVA research coordinator will be notified and then open the next sealed envelope in the assignment sequence; the group assignment for that participant to one of the two groups will be revealed at that point. In this fashion, only the postdoctoral fellow interventionist assigned to provide REACH TBI will know the group assignment of a specific TBI caregiver. Because the intervention will be delivered by trained personnel who will have minimal contact with the waitlist control group (other than during the randomization call when the caregiver is informed of their study arm), we anticipate minimal overlap or “contamination” between these interventions and waitlist control group participants. Although participants and interventionists cannot be blinded during the study, all research staff involved in data collection and biostatistics staff involved in formal statistical analyses will be blinded to reduce bias and preconceptions in collecting and analyzing data.

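### Exclusion 3 bars only caregivers who completed an earlier REACH version, so a caregiver now receiving another version can be randomised, which could dilute the 3-month contrast

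*Protocol article*

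**What the plan says.** The Protocol article lists seven inclusion and three exclusion criteria under Participants, Recruitment, and Sample Size. The third exclusion is to "have completed a previous version of the REACH intervention". No other criterion concerns past or present use of REACH.

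The Introduction describes REACH VA, delivered in 4 or 6 sessions, as "a VA national program for dementia [27], spinal cord injuries and disorders [28], multiple sclerosis [29], and posttraumatic stress disorder caregivers [30". It also reports, for Veterans and Service Members with TBI, "high rates of particular comorbid conditions (eg, posttraumatic stress and pain", without giving a percentage.

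Under Randomization, the article says that "we anticipate minimal overlap or “contamination” between these interventions and waitlist control group participants". The reason given is that the trial's own interventionists have little contact with the waitlist arm.

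The sample size is based on the between-group comparison at 3 months with baseline as covariate (Preliminary Analyses). Under Secondary Quantitative Analyses, the control group is not expected to improve over those 3 months.

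**The concern.** By excluding completers, the plan accepts that earlier REACH exposure matters. The word *completed* then leaves out the caregivers whose exposure falls most directly in the comparison period: those receiving another REACH version at screening. A site applying the list as written would have to accept such a caregiver, provided that the other criteria were met.

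The route is plausible from the article alone. The existing program and the trial draw on the same health system, and the posttraumatic stress version serves an overlapping set of families. REACH TBI is built from the foundational REACH tools and shares its core components of problem-solving, cognitive reframing and stress management (Intervention Development; Intervention).

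An active REACH user on the waitlist could improve before month 3, when controls are meant to be untreated. An active user in the immediate arm could gain less from REACH TBI on top of the other version. Both pull the arms together. Because the analysis is by intention to treat, these caregivers stay in the comparison once randomised.

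**Working it through.** **Inputs from the article** (Participants, Recruitment, and Sample Size): d = 0.50; pre–post correlation r = 0.50; two-sided alpha 0.05; 80% power; 10% attrition; 55 randomised per group.

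**Inputs not in the article, so assumed:** f, the share of randomised caregivers currently using another REACH version (5% or 10%; of 110, that is 5.5 or 11 caregivers), and L, the share of the treatment contrast lost in each of them (half or all).

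**Step 1: reproduce the plan's figure.**
- Residual SD after baseline adjustment: √(1 − 0.50²) = 0.866.
- Normal approximation: n = 2 × (1.960 + 0.842)² × 0.75 / 0.50² ≈ 47.1, so 48 evaluable per arm; 48 / 0.90 = 53.3, so 54 randomised.
- Noncentral t: 49 evaluable per arm; 49 / 0.90 = 54.4, so 55 randomised, which matches the plan.
- Evaluable at the planned size: 55 × 0.90 = 49.5 per arm. SE = 0.866 × √(2/49.5) = 0.174. Power is 81.9% (normal) or 81.2% (t).

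The sample size is correct on its own assumptions, with 1 to 2 points to spare above 80%.

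**Step 2: dilute the contrast.** Mean contrast = 0.50 × (1 − f × L). Power (normal) = Φ(contrast / 0.174 − 1.960).

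| f | L | Contrast (SD) | Power, normal | Power, t | Randomised per group for 80% (normal) |
|---|---|---|---|---|---|
| 0 | – | 0.500 | 81.9% | 81.2% | 54 |
| 5% | half | 0.4875 | 80.0% | 79.2% | 56 |
| 5% | all | 0.475 | 77.9% | 77.1% | 59 |
| 10% | half | 0.475 | 77.9% | 77.1% | 59 |
| 10% | all | 0.450 | 73.4% | 72.5% | 66 |

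On the normal approximation, 5% exposed with half the contrast lost uses up the margin over 80%.

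**Step 3: direction.** Randomisation spreads such caregivers over both arms. If REACH TBI has no effect beyond what the arms share, their presence creates no systematic difference. The cost is power, not a raised false-positive rate.

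**The case against.** The strongest reply is that exposure is probably limited. The article states that "REACH has never been tailored specifically for or tested in caregivers of V/SMs with TBI", and its Discussion says that these caregivers have no structured national intervention. Participants must "believe that at least half of their caregiving responsibilities are likely related to TBI rather than another health condition or conditions", which selects away from caregivers whose role is mainly about another condition. The Zarit threshold of 8 removes those already helped enough to fall below it. A REACH course is short, so few caregivers would be mid-course at screening. All of this stands as a reason to expect a small f. It does not close the gap: up to half of the caregiving may still concern another condition, and high burden is compatible with being in REACH now.

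A reader might infer several stronger points that the article does not support:

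- *That the wording does shrink the contrast.* This depends on f and L, and the article gives neither. High rates of posttraumatic stress among Veterans and Service Members say nothing about how many of their caregivers use REACH.
- *That caregivers who stopped REACH partway contaminate the waitlist.* They receive no new sessions during months 0 to 3. Any lasting benefit is largely in the baseline score, which is in the model, and randomisation balances them in expectation. At most, such caregivers in the immediate arm might gain less.
- *That the contamination statement under Randomization is wrong.* It concerns spill-over between the trial's arms and makes no claim about outside programs.
- *That the comparison is with a strictly REACH-free control.* The stated comparator is a waitlist control within an effectiveness-implementation design, where some background service use is compatible with the aim.

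**Conclusion.** The point holds in limited form. As written, exclusion 3 allows a caregiver currently receiving another REACH version to be randomised. In the waitlist arm this could dilute the powered 3-month contrast and cost power.

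The size cannot be determined from the article. On the assumed values, power falls from about 82% to 78–80% at 5% exposed and to 73–78% at 10%. The lower figure in each range assumes that the whole contrast is lost in every exposed caregiver, which is a worst case for a version not adapted to TBI. The calculation also takes the plan's own effect size, correlation and attrition as given, and treats the 3-month contrast as a baseline-adjusted comparison of two means.

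This is not an error in the sample size, nor a demonstrated bias. It is a gap in a stated rule that is cheap to close.

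**What to change.** Reword exclusion 3 along these lines: *have completed, or are currently enrolled in, any version of REACH*. This needs one eligibility phrase and one screening question. The downside is a slightly smaller eligible pool. With current users excluded, the dilution they would bring is avoided and 55 per group can stand.

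Optionally, record earlier partial REACH use and any REACH sessions received outside the trial, including any begun after randomisation, which an eligibility rule cannot prevent. These data would support a sensitivity analysis, with the intention-to-treat result kept primary. The full protocol or analysis plan may already cover this, so its absence from the article is not a fault.

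Excluding everyone who ever started any version would go further than needed. It would remove, for example, a caregiver who had a single session years ago, and that is a trade-off against generalisability for the investigators to judge.

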### Ethical Considerations

The UVA institutional review board (IRB) will be overseeing research activities carried out at all civilian research universities (UVA IRB-SBS Protocol # 6237). The University of South Florida (USF) is the reliance-agreement IRB of the James A. Haley Veterans’ Hospital and will be responsible for the oversight of the work occurring at this VA Medical Center (USF IRB Study # 006569). Using the VA’s corporate data warehouse, Veterans will be identified with a TBI diagnosis. Recruitment of their caregivers will be conducted remotely by research coordinators, who will screen potential participants for eligibility. Participants must give permission to be screened after hearing a study description that includes the components of informed consent including information about the study and the screening process itself. Study components will include a statement of the research (purpose, procedures), reasonably expected benefits to participants, and costs. The screening process components will include the duration of screening, alternatives, extent of confidentiality, and authorization for the release of protected health information for research purposes.

After the screening, consent forms, signed by the consenting research coordinator, will be emailed via secure Docusign (Docusign, Inc) or mailed with a postpaid return envelope, depending on the preferences of the caregiver. Informed consent will follow procedures of the UVA IRB (UVA IRB-SBS Protocol # 6237), USF IRB (USF IRB Study # 006569), and Research and Development Committee of the Tampa VA. Participants must give written or electronic informed consent before enrolling. During the informed consent call, the potential participant will be asked to read the informed consent and be given the opportunity to ask questions. A research coordinator will review all key aspects of the study with the potential participant and question to ascertain whether the potential participant has understood the information.

After consent is obtained and baseline data collected, participants will be randomly assigned to the immediate intervention group or waitlist control group. Each caregiver will be offered US $25 for each completed data collection and the exit interview for a total of US $100 (immediate intervention group) or US $125 (waitlist control group).

### Randomization

A block randomization schedule [42] (with 6 participants per block) will be created with a web-based computerized random number generator. The UVA research coordinator will maintain allocation concealment and eliminate possible selection or recruitment biases by keeping the randomization schedule concealed from the on-site research coordinator engaged in recruiting. The randomization schedule will be generated by the UVA research coordinator who will not have any contact with participants, and sequentially numbered sealed envelopes will be prepared prior to the recruitment of any participants. After the recruiting research coordinator determines eligibility for a prospective dyad and obtains informed consent, the UVA research coordinator will be notified and then open the next sealed envelope in the assignment sequence; the group assignment for that participant to one of the two groups will be revealed at that point. In this fashion, only the postdoctoral fellow interventionist assigned to provide REACH TBI will know the group assignment of a specific TBI caregiver. Because the intervention will be delivered by trained personnel who will have minimal contact with the waitlist control group (other than during the randomization call when the caregiver is informed of their study arm), we anticipate minimal overlap or “contamination” between these interventions and waitlist control group participants. Although participants and interventionists cannot be blinded during the study, all research staff involved in data collection and biostatistics staff involved in formal statistical analyses will be blinded to reduce bias and preconceptions in collecting and analyzing data.

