To ensure prompt reporting of research-related events, we will follow IRB guidelines. As soon as possible but in all cases within 1 to 5 working days, the PI will report to the IRB any changes to the protocol that were taken to eliminate hazards to a research participant, deviations to protect the physical well-being of a participant in an emergency, and any serious adverse event, related or possibly related to the research regardless of whether the event occurred during the study. Participants will have access to call study personnel and the PI during normal business hours to report concerning effects. A more thorough investigation of adverse effects will be performed as needed. While we do not anticipate serious adverse events that call for emergency care, if emergency care is required during a study visit, study staff will contact emergency services, and study staff will work with the participant to obtain such care. It will be emphasized to participants that they can take a break or discontinue either data collection or the REACH sessions at any time. An individual’s participation in the study will be terminated if the participant wishes to stop their participation in the study or in response to any significant adverse event determined by staff to warrant stopping study treatments. If the V/SM objects to their caregiver participating, this can also be a reason for discontinuation.

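### A constant, published block size of 6 would make about a quarter of assignments certain, on average, if the recruiter learned all earlier arms in a block; varying the size is a cheap second safeguard

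*Protocol article*

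**What the plan says.** The Randomization section of the Protocol article specifies a block schedule "with 6 participants per block) will be created with a web-based computerized random number generator". It is one sequence: after consent, the off-site coordinator is to "open the next sealed envelope in the assignment sequence". No strata, site lists or other block sizes are mentioned. The section on sample size gives the allocation: "55 participants will be randomized to each group (N=110".

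The same section sets out the safeguards. The coordinator who makes the list has no contact with participants. Numbered envelopes are sealed before recruitment starts and opened only after eligibility and consent. The plan relies on "keeping the randomization schedule concealed from the on-site research coordinator engaged in recruiting" and says this will eliminate selection and recruitment bias. It adds that "only the postdoctoral fellow interventionist assigned to provide REACH TBI will know the group assignment of a specific TBI caregiver".

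On blinding, the section begins "Although participants and interventionists cannot be blinded during the study" and then states that data collectors and statisticians will be blinded. Caregivers learn their arm in a randomization call. The Setting section says that the Tampa hospital "is the data core where recruitment and data collection will be conducted", so recruiters and data collectors share a core. The interventionist works in a different one.

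**The concern.** With a constant block of known length, the end of each block is determined by its beginning: once three caregivers in a block have gone to one arm, the rest must go to the other. The safeguards hide the schedule. They cannot hide an assignment that a caregiver mentions, and caregivers know their arm. A recruiter who had heard the earlier arms and counted enrolments would sometimes know the next arm before approaching anyone. Opening the envelope after consent does not help against that.

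At stake is selection: who is approached, when, and how warmly. The primary outcome is self-reported strain. The baseline score is in the primary model, so steering on measured strain would be at least partly adjusted for. Steering on motivation or readiness to engage would not be.

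**Working it through.** **Inputs.** Block size 6, one sequence (Randomization). Equal groups, N = 110, d = 0.50, r = 0.50, 80% power, two-sided 0.05, 10% attrition (Participants, Recruitment, and Sample Size). Recruitment over 18 months (Study Design). First follow-up at 3 months (Quantitative Data Collection). The 3:3 split within a block is implied by equal allocation, not stated.

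**The plan's own figure.** The article gives no figure for predictability; its only computable figure is N. With baseline adjustment, n per arm = 2 × (1.96 + 0.84)² × (1 − 0.5²) / 0.5² ≈ 47.1, so 48 (49 with the t distribution). Dividing by 0.9 gives 54 (or 55). The stated 55 per group is reproduced, and 110 can be used below.

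**Forced assignments when all earlier arms in the block are known.** A 3:3 block has 20 arrangements. Count the positions at which one arm is already used up:

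| Forced positions | Arrangements | Share of the block |
|---|---|---|
| 1 | 12 | 16.7% |
| 2 | 6 | 33.3% |
| 3 | 2 | 50% |

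Mean = (12×1 + 6×2 + 2×3) / 20 = 1.5 per block, and 1.5/6 = 25%. This is an average and not a ceiling.

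For N = 110 there are 18 full blocks and 2 left over. The last two cannot be forced, so the expected total is 18 × 1.5 = 27, or 24.5%. The variance per block is (12×1 + 6×4 + 2×9)/20 − 1.5² = 0.45, so the SD of the total is √(18 × 0.45) ≈ 2.8.

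**Best guess.** Always guessing the arm with more places left is right 4.1 times in 6, or 68.3%, against 50% by chance.

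**Partial leakage.** An assignment is certain only if the recruiter knows the arms of all three members of the exhausted arm. If each arm leaks independently with probability q (an assumption; the article gives no rate), the share is 25% × q³:

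- q = 1: 27 × 1 = 27 assignments
- q = 0.5: 27 × 0.125 ≈ 3.4 assignments
- q = 0.2: 27 × 0.008 ≈ 0.2 assignments

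**Timing.** 110 / 18 ≈ 6.1 enrolments a month, so on average a block fills in about one month. An arm disclosed at the 3-month contact, or through the 9-month collection that only waitlist caregivers have, would normally belong to a block already closed. Only earlier disclosure matters. The possible routes are:

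- *Unscheduled contact.* The section on adverse events says "Participants will have access to call study personnel and the PI during normal business hours", but for reporting concerning effects, and nothing says that the recruiter takes the call.
- *Alert handling.* Alerts are dealt with in the randomization call for waitlist caregivers, and in that call plus session 1 for treated ones. The form is then filed in a shared folder. The article does not say who can open it, so this is a possible route and not a shown leak.

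**Effect of varying the size.** In 3,000 simulated sequences of 110, the guesser knew every past arm and the set of possible sizes, and sizes were drawn with equal probability:

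| Sizes | Certain | Best guess right |
|---|---|---|
| 6 only | 24.5% | 68.1% |
| 4, 6 | 5.6% | 69.2% |
| 4, 6, 8 | 2.3% | 67.9% |

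Varying the size removes nearly all certain deductions (0.023 × 110 ≈ 2.5 left) and hardly changes the guessing rate.

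**Balance.** 110 is not a multiple of 6. The last two participants split evenly with probability 2 × (3/6) × (3/5) = 0.6, so the present scheme does not guarantee 55 per group either.

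**The case against.** The strongest reply is that the plan already protects what matters. The list is made off site by someone who never meets participants, the envelope is opened after consent, the interventionist sits in another core, and data collectors are to be blinded. The 25% and 68% figures assume that these measures have failed for nearly every member of a block, within weeks. A fixed block with off-site assignment after consent is an accepted design, and nothing in the article is contradictory here.

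Most of this stands. If the safeguards hold, the effect is nil, and the routine follow-up contacts come too late to matter. What remains is that the safeguards govern staff and documents, while caregivers know their arm and can mention it. The block size is the one element that turns such remarks into certainty.

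Three stronger readings are tempting, and the documents do not support them:

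- *Concealment has failed.* No leak is described.
- *The trial is unblinded throughout.* Only participants and interventionists are.
- *Varying the block size would remove the risk.* The best-guess rate stays near 68% when past arms are known.

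**Conclusion.** This is a minor, conditional weakness and worth a cheap improvement. With complete knowledge of the earlier arms in each block, about a quarter of assignments on average (about 27 of 110) would be certain before consent. With partial leakage the number falls with the cube of the leak probability, and with no leakage it is zero. The figures assume 3:3 blocks, a recruiter who counts enrolments, and disclosure within about a month of randomization. No bias in the treatment effect is quantified, and the article gives no basis for doing so.

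**What to change.** Generate the list, or its unused part if recruitment has started, with randomly varying block sizes, for example 4, 6 and 8. Keep the sizes from recruiting and data-collection staff until recruitment ends. The size of 6 is already published, but it tells a recruiter little once sizes vary.

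Keep past assignments away from recruiters as now, since that remains the main protection.

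The cost is a new list and, if recruitment is under way, new envelopes for the remaining numbers. A last block cut short can leave the groups a few participants apart: at most 4 with a block of 8 (57 against 53), compared with at most 2 now.
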